### Measurements

At baseline patients will complete seven questionnaires, regarding self-management activities, food habits, physical activity, health status, quality of life, diabetes dependent quality of life and diabetes treatment satisfaction. For a detailed description of the questionnaires see Table 2. Patients are asked to complete the baseline questionnaires before randomisation. After 3 months (T3) patients will complete two questionnaires; after 6 months (T6) patients will complete eight (control group) to nine (intervention group: extra questionnaire on satisfaction with the app) questionnaires (see Table 2). Patients in the intervention group also complete one questionnaire after 9 months of follow-up (T9) (see Table 2). All clinical variables are obtained by an online case report form (eCRF) completed by the practice nurse or diabetes nurse at T0, T6 and for the intervention group also at T9. In addition to anthropometric (length, weight, waist circumference and blood pressure) and laboratory parameters (HbA1c and lipid profile), the following demographic and clinical variables are collected: age, duration of diabetes, ethnicity, level of education, smoking status (current, former, never), presence of microvascular complications (nephropathy, retinopathy, neuropathy) and macrovascular complications (cardiovascular diseases), and diabetes medication use (including insulin injection frequency and dose).

**Table 2 Tab2:** Description of questionnaires

Questionnaire	Description	Score range	Completed at
Summary of Diabetes Self-Care Activities Measure (SDSCA) [34]	11 Items assessing several aspects of the diabetes regimen: diet, exercise, blood glucose testing, foot care and smoking. Items measure how many days a patient has performed self-care activities in the last 7 days.	10 Items rated on an 8-point Likert scale, measuring how many days an activity is performed in the last week. One item measures smoking status (yes/no) and the amount of cigarettes smoked in the last week. Each of the domains is measured separately.	T0, T6
Food habits questionnaire (FFQ) [35]	18 Items assessing patient’s habits with regard to preparation of food, fatty food intake, dietary products and fruit and vegetable intake.	All items differ in the scoring ranges, varying from four scoring options (never, sometimes, frequently or always) to eight options (never to 7 days a week)	T0, T6
International Physical Activity Questionnaire (IPAQ) [36]	25 Items assessing how many days physical activities are performed during the past 7 days in four domains (work, transportation, housework and leisure-time), 2 items assess sedentary behaviour.	Total physical activity score is calculated as the sum of the number of minutes of total moderate activity for each subdomain, plus two times the number of minutes of total vigorous activity for each subdomain.	T0, T6
EQ-5D-5 L [37]	Quality of life questionnaire. The classification system (EQ-5D-Profile) covers mobility, self-care, daily activities, pain/discomfort and anxiety/depression. The Visual Analogue Scale (EQ-5D-VAS) is a graduated, vertical line, anchored at 0 (worst imaginable health state) and 100 (best imaginable health state).	For the EQ-5D-Profile each domain has five levels of functioning: from no problems to severe problems. For the EQ-5D-VAS the patient is asked to rate his/her health by marking a point on the EQ-5D-VAS that best reflects his/her actual health state.	T0, T3, T6, T9^a^
The Short Form (36) Health Survey (SF-36) [38, 39]	Generates a profile of scores on eight dimensions of health status: Physical Functioning (10 items), Role Physical (4 items), Bodily Pain (2 items), General Health (6 items), Vitality (4 items), Social Functioning (2 items), Role-Emotional (3 items) and Mental Health (5 items).	The different scales can be summarized in two component scores: the Physical Component Score and the Mental Component Score. Both scores range from 0 (least favorable health state) to 100 (most favorable health state).	T0, T6
The Audit of Diabetes-Dependent Quality of Life (ADDQoL) [40]	A measure of impact and importance of diabetes and its treatment on quality of life. The ADDQoL consists of 19 diabetes-specific items and two overview items. For each item the patient is asked how things would be without diabetes, with an impact rating and an importance rating.	The impact rating ranges from − 3 (very much better) to 1 (worse), the importance rating ranges from 3 (very important) to 0 (not at all important). The average weighted impact ADDQoL score is the sum of all the weighted impact scores in the nominator and of the number of domains in the denominator, and ranges from − 9 to 3.	T0, T6
Diabetes Treatment Satisfaction Questionnaire (DTSQ) [41]	Includes 8 items. In question 1 and 4–8 the satisfaction with the treatment is better if the scores are higher. In questions 2 and 3, lower scores indicate blood glucose levels closer to the ideal, and higher scores indicate problems.	Scores range per item from 6 (very satisfied) to 0 (very dissatisfied); total score range 36 to 0.	T0, T6
Satisfaction and usability of the app	Questionnaire newly developed by the researchers contains questions about the satisfaction with regard to receiving app-triggers, frequency, timing and comprehensibility, see Additional file 1.	All items will be rated on a 5-point Likert scale.	T6^a^
Outpatient clinic visits and paramedical health care use	Newly developed questionnaire contains one question on outpatient clinic visits (for patients recruited from primary care) or GP visits (for patients recruited from hospitals) and three questions on paramedical health care use: whether patients have visited a dietician, a physiotherapist or a specialised feet therapist the past 3 months.	All four questions are answered with yes or no. In case of a ‘yes’, patients have to fill in how many times they have visited the physician/therapist.	T3, T6

Abbreviations: *T0* baseline measurement, *T3* measurement after 3 months of follow-up, *T6* measurement after 6 months of follow-up, *T9* measurement after 9 months of follow-up

^a^Completed by intervention group only

For the cost-effectiveness analysis, data on health care use are extracted from both the electronic medical record and from the questionnaires sent to the participants at T3 and T6. The number of hypoglycaemic events and the glycaemic variability are extracted at T6 (control group and intervention group) and at T9 (intervention group) from patient diaries, handed out to the patients at the start of the study. These diaries are designed for the purpose of this study only: patients record information on all hypoglycaemic events during the study, and once a week blood glucose values throughout the day (fasting plasma glucose and three pre-prandial values). For an overview of the study design and procedures: see Fig. 3.

**Fig. 3 Fig3:**
[figure not shown]
A schematic diagram with an overview of the study design and the main procedures

### Monitoring, safety and confidentiality

A monitor will assess the safety and validity of the research data. Due to the low risk character of the intervention, only spontaneously reported adverse events will be reported in the result paper. Research data will be stored in code: all participants will receive their own serial number based on the study site and the eCRF number. Clinical data of the participants will be extracted from electronic medical records and anonymously provided on an eCRF to the coordinating research center.

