**Fig. 2 Fig2:**
[figure not shown]
TRIGGER app home screen. Translation: contact onderzoekers = contact information; informatie studie = study information; instellingen = settings; voeding = nutrition; beweging = physical activity; hypo’s voorkomen = preventing hypoglycaemia; glucose regulatie = glucose regulation

**Table 1 Tab1:** Examples or app messages

Category	Message
Dietary habits	- Fruit juices are not as healthy as many people think: they contain lots of sugar and calories. Try to consume fruit juices as infrequently as possible, eat fruit instead! - Don’t drink any soda today. Choose water, or tea or coffee without any sugar instead.
Physical activity	- Take the stairs instead of the elevator, wherever you are. Or take the elevator to one floor below and take the last stairs. All steps count! - People with a healthy weight are advised to be physically active for at least 30 min a day. People who are overweight are advised to have at least 60 min of physical activity each day.
Prevention of Hypoglycaemia	- Instruct your spouse, family, neighbour, colleague or a friend on how they should act when you have a hypoglycaemic event. - Do you have nocturnal hypoglycaemic events? Ask your doctor whether it is advisable to adjust your insulin dose.
Glucose variability	- Never inject insulin into the tough skin of insulin-induced lumps; because of slower absorption there, this may lead to blood glucose fluctuations. - When you have high blood glucose levels, it is important to drink a lot (1.5–2 l sugar free beverages per day) and to take your medication properly.

Users will receive a push notification to direct them to open the app when a new app-trigger is available. When the app is not opened in the following 24 h, a reminder SMS is sent: the SMS fall-back system. The number of reminder SMSs will be monitored.

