The timing of the messages is either at random times between 9.30 a.m. and 8.00 p.m. or at times associated with the content of the message (e.g. messages containing advice for dinner are sent in the morning or early afternoon in order to get the receiver to adapt to that advice). The intervention will be tailored to the patients’ preferences, they can choose on:The topics: hypoglycaemia will be a mandatory topic, it should be combined with at least two of the following topics: dietary habits, physical activity or glucose regulation (including glycaemic variability).The frequency: two or six times per week, one app-trigger per day. The option to prolong the intervention with another 3 months after the first 6 months. During this period the patient will receive app-triggers with unaltered frequency and topics.

Apart from receiving app-triggers, the intervention group will receive usual care for their T2DM.

Patients randomised to the control group receive usual care according to the Dutch primary care guidelines, that advise two to four diabetes monitoring visits per year [2]. Through diabetes education from either the GP or the practice nurse, patients learn about target values for glycaemic control, lipids and blood pressure, a healthy lifestyle, recognising hyperglycaemic or hypoglycaemic episodes and how to respond to these episodes. Patients randomised to the control group are not able to use the smartphone app we developed. To increase the participation rate, patients in the control group will be given the opportunity to use the app after the study has ended.

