### Concealment of allocation and blinding

The study is not blinded at patient level because of the nature of the intervention, which requires overt participation. The practice nurses/diabetes nurses/outcome assessors are also not blinded to patient allocation.

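### Adverse events other than diary-recorded hypoglycaemia are published only if volunteered, in an unblinded trial with unequal messaging and follow-up, so counts may not be comparable between arms

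*Protocol article*

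**What the plan says.** Under Monitoring, safety and confidentiality, the protocol article says that "only spontaneously reported adverse events will be reported in the result paper". The reason comes just before: "Due to the low risk character of the intervention". No time window is attached to the rule.

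Four other parts of the article bear on how this rule would work:

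- **Blinding** (Concealment of allocation and blinding): "The study is not blinded at patient level because of the nature of the intervention", and "The practice nurses/diabetes nurses/outcome assessors are also not blinded to patient allocation".
- **Contact through the app** (The intervention): app-arm patients receive at least two and at most six messages a week, with hypoglycaemia as a compulsory topic. For the other arm: "Patients randomised to the control group are not able to use the smartphone app we developed".
- **Follow-up** (Measurements): the clinical case report form is "completed by the practice nurse or diabetes nurse at T0, T6 and for the intervention group also at T9".
- **Hypoglycaemia** (Measurements): patients note every event in a study diary. The number of events and the glycaemic variability "are extracted at T6 (control group and intervention group) and at T9 (intervention group) from patient diaries".

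Table 2 shows what both arms are asked at T3: the EQ-5D-5L and a short questionnaire on outpatient or GP visits and on visits to a dietician, physiotherapist or foot therapist. Both are repeated at T6. Neither is described as asking about hospital admission, emergency care or other harm.

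**The concern.** A spontaneous report needs an event and also a decision to mention it. That decision can depend on how often the patient is reminded of their health, how long the patient stays in contact with the study, and whether patient and nurse know the allocation. Here the first two differ by arm by design, and the allocation is known to everyone involved.

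A results paper of a two-arm trial that lists adverse events by arm invites a comparison, whether or not one is formally tested. An excess under the app could reflect more reporting rather than more harm. Similar counts could hide a real difference, or under-reporting in both arms. For events outside the diary, the low risk that justifies the rule would then remain largely an assumption that the trial does little to test.

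**Working it through.** **1. Which harms the rule governs.** Hypoglycaemia is part of the co-primary outcome and a secondary outcome at 6 months. It is recorded by diary in both arms, extracted at T6 in both arms, and has a planned Poisson regression (Outcomes; Measurements; Analysis). It does not depend on volunteering. The rule therefore matters for all other adverse events.

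**2. The plan's own figure.** The article gives no expected adverse-event rate. The only design figure used here is the group size. A two-sample t-test with difference 0.41, SD 1.1, 5% two-sided and 80% power needs 113.96 per arm, so 114, as stated under Sample size. (Sidedness is not stated; a one-sided calculation gives 90 and does not match.)

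**3. Observation time, with everyone followed to the end.**

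- App arm to T9: 114 × 9 = 1026 patient-months.
- Control arm to T6: 114 × 6 = 684 patient-months.
- Ratio: 1026 / 684 = 1.5. App-arm share: 1026 / (1026 + 684) = 1026 / 1710 = 60%.

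This applies only if events after T6 are counted in the comparison.

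**4. Time and reporting together.** Expected reports per arm = 114 × m × r × p, where m is months observed, r the true event rate per patient-month (set equal in both arms) and p the probability that an event is volunteered. The rate cancels from the ratio:

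ratio = (m_app × p_app) / (m_control × p_control)

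The values of r and p below are assumptions for illustration; the document gives neither. Expected reports use r = 0.02.

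| Months, app / control | Reporting, app / control | Expected reports, app / control | Ratio |
|---|---|---|---|
| 6 / 6 | 30% / 30% | 4.1 / 4.1 | 1.0 |
| 6 / 6 | 40% / 30% | 5.5 / 4.1 | 1.33 |
| 6 / 6 | 60% / 30% | 8.2 / 4.1 | 2.0 |
| 6 / 6 | 30% / 40% | 4.1 / 5.5 | 0.75 |
| 9 / 6 | 30% / 30% | 6.2 / 4.1 | 1.5 |
| 9 / 6 | 40% / 30% | 8.2 / 4.1 | 2.0 |
| 9 / 6 | 60% / 30% | 12.3 / 4.1 | 3.0 |

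Example: 114 × 9 × 0.02 × 0.3 = 6.2 and 114 × 6 × 0.02 × 0.3 = 4.1. At r = 0.05 the same row gives 15.4 and 10.3; the ratio stays 1.5.

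**5. Reading the table.** Equal windows and equal reporting give 1.0, so a distortion is possible but not certain. If app patients volunteered less than controls, the ratio would fall below 1 (0.75 in the fourth row). A 6-month cut-off removes the factor of 1.5 but leaves any difference in reporting untouched. Only asking both arms the same question at the same times addresses that part.

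**The case against.** The strongest reply is that the rule is openly declared, a reason is given, and the intervention is text messages. The harm that matters most in insulin users is collected by diary in both arms. A reader might take the rule to mean that all harms are recorded only when volunteered; the diary shows that this is not so.

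A reader might also infer that the app arm will show 1.5 times as many events. The document does not support that. The between-arm outcomes are set at 6 months, T9 serves a comparison within the intervention group only, and no sentence puts later adverse events into a comparison of arms. Nor is a formal between-arm test of adverse events announced. What remains is that, unlike the outcomes, adverse events are given no window.

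Two further inferences fail. The home-screen item in Fig. 2 is explained only as "contact onderzoekers = contact information"; no reporting function is described, and nothing says that controls lack other ways to reach the researchers or nurses. And the sentence on the monitor concerns whether the research data are safe and valid; it promises no interim review of events, so the timing of diary extraction does not contradict it.

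It is also fair to say that the messages steer patients to their own care providers, not to the trial, that usual care teaches patients to recognise hypoglycaemia, and that no figure in the document shows differential reporting. Health care use is extracted from medical records too, though for the cost-effectiveness analysis. Finally, the full protocol may hold procedures for serious events that a journal article omits. That does not remove the point, because what the results paper will contain is stated here.

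**Conclusion.** The point holds in a limited form. For adverse events other than diary-recorded hypoglycaemia, the plan commits to publishing volunteered reports only, under conditions that differ between arms: recurring messages in one arm, longer follow-up in that arm, and no blinding in either. Such counts may not be comparable.

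The size is not fixed by the document. It is 1.0 with equal windows and equal reporting, 1.5 if events to T9 were pooled with equal reporting, and 1.33 to 2.0 within 6 months under the assumed reporting of 40% to 60% against 30%. With pooling and that reporting difference together it would be 2.0 to 3.0. The direction is open as well. These ratios assume equal true event rates and complete follow-up of 114 patients per arm. The HbA1c analysis and the diary-based hypoglycaemia outcomes do not depend on this rule.

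**What to change.** Change the rule under Monitoring, safety and confidentiality in three respects:

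1. Put the same short harm question to both arms in the online questionnaires already sent at T3 and T6. It could cover, for example, hospital admission, emergency care, and hypoglycaemia needing another person's help since the previous questionnaire (at T3, since the start of the study).
2. Report the between-arm harm comparison for T0–T6 only, with solicited events shown separately from spontaneous ones.
3. List app-arm events from T6 to T9 separately and keep them out of the comparison.

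If the question cannot be added, the second and third changes still apply as far as the window goes, with a statement that spontaneous counts are not comparable between arms.

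The cost is slightly longer questionnaires and a few more answers to process; no extra visit is needed. Answers would still be self-reported by patients who know their allocation, so the change equalises the question and the time window but does not remove the effect of that knowledge.

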### Concealment of allocation and blinding

The study is not blinded at patient level because of the nature of the intervention, which requires overt participation. The practice nurses/diabetes nurses/outcome assessors are also not blinded to patient allocation.

### Sample size

Based on the decrease in HbA1c in previous mHealth studies [9, 10, 18, 21, 31], we expect a mean difference in HbA1c level of 0.41% with a standard deviation of 1.1% between the intervention group and the control group after 6 months. To detect this difference in the primary outcome with an 80% power and a non-significant difference of 5% after 6 months, 228 T2DM patients (114 per treatment group) are needed. We used SAS version 9.4 (SAS Corp., Cary NC) for the sample size calculation.

### Analysis

Age and sex of our study population will be compared to those who declined to participate to investigate selection (bias). We will also compare baseline characteristics of our study population to those of similar Dutch T2DM patient cohorts.

Intention-to-treat analysis will be performed for the primary and secondary outcomes. If necessary, a multiple imputation technique will be used to handle missing data.

To analyse continuous variables we will use general linear models. Binary outcome variables will be analysed with logistic regression. To analyse the number of hypoglycaemic events we will use a Poisson regression. If necessary, the analysis will be adjusted for overdispersion or underdispersion.

Firstly, we will perform a univariable analysis to examine the intervention effect. Afterwards we will perform a multivariable analysis corrected for the following baseline characteristics: baseline value, age, sex, duration of diabetes and insulin dosage.

### Cost-effectiveness analysis

The cost-effectiveness of the intervention will be determined from a healthcare perspective. EQ-5D-5 L will be used to calculate quality-adjusted life-years (QALYs), following an area under the curve approach, with interpolation between measurements. All health care use will be valued following standard costs per unit as advocated for use in Dutch health economic evaluations. Cost differences between intervention and control groups will be related to QALY differences between groups. A probabilistic sensitivity analysis will be performed using bootstrapping. Results will be presented graphically in Cost-effectiveness Acceptability Curves.

## Discussion

Self-management is crucial for T2DM patients, especially for those on insulin therapy. However, to be effective, self-management education should be intensive [32], and thus will be costly. Moreover, worldwide there is a rapid increase in the number of T2DM patients. Against that background, cost-effective solutions to promote diabetes self-management are pivotal. If our newly developed app proves to be cost-effective, it could be used by all insulin treated T2DM patients because the messages are evidence-based and not region-specific. The topics ‘dietary habits’ and ‘physical activity’ can also be used to stimulate diabetes self-management in the non-insulin users. The app may be a standalone intervention but can also be used as part of a more comprehensive program. A possible limitation for delivery at scale might be the attitude of health care providers towards new technologies. Whereas the use of automated unidirectional messages may seem simple, a recently conducted systematic review and meta-analysis on this topic showed that one-way and two-way messages had a very similar effect, while two-way messages are usually more resource intensive [33].

An operational issue that may occur during the study is that patients stop reading the text messages, while they are not formally withdrawn from the study. However, since we are able to monitor the number of reminder SMSs sent (SMS fall back), we will be able to monitor the ‘adherence’. Moreover, this study is a real-life pragmatic trial; in real-life we also expect non-use or infrequent use of a smartphone app. Another issue that may arise, is that because all patients are informed about the study before they sign informed consent and before they are randomised, patients in the control group may also get aware of the existence of diabetes apps. Some patients in the control group might start using other diabetes apps during the study. To overcome this, patients in the control group will not have access to the smartphone app developed for the purpose of this trial, but will be offered to use it immediately after. Besides, both patients in the intervention and control group are equally able to use other diabetes apps.

Barriers to the adoption of the intervention among study participants may play a role. It is possible that this intervention is less effective among certain subpopulations that may be considered hard to reach (i.e. men, low socio-economic status and those who do not regularly attend health services). For that reason we will look at selection bias. This trial will include a relatively high number of T2DM patients, as suggested by a recent reviews [8, 19, 33]. It will add to the evidence base for mHealth interventions to stimulate self-management in insulin treated T2DM patients. The results may be of interest for health care providers, patients, patient organisations and policy makers who aim to increase diabetes self-management.

